### Results from early-phase prospective trial: the NEXTAC-ONE study

We reported a phase I study to evaluate the feasibility of multimodal interventions, including exercise and nutritional intervention, for elderly patients with advanced NSCLC or pancreatic cancer [16]. That study was named the “NEXTAC (Nutrition and Exercise Treatment for Advanced Cancer)-ONE” study and was performed as a prospective single-arm study to assess the feasibility of early nonpharmacological, multimodal interventions (NEXTAC program). The NEXTAC program was designed specifically for elderly cancer patients with high cachectic potential, and it consists of nutritional sessions, exercise educational sessions (muscle training and physical activity), lifestyle consultations and daily oral nutritional supplements (Inner Power®) that were implemented over an 8-week study period. We hypothesized that it is possible to initiate the NEXTAC program in the early treatment phase in elderly patients with advanced cancer, and we conducted the phase I study. The primary endpoint of the study was the participation rate, which was measured at three points during the 8-week study period. The three assessment points were as follows: at the time of study entry and 4 ± 2 weeks and 8 ± 2 weeks after the intervention started. In addition to the participation rate in the NEXTAC program, the physical activity level of each participant was evaluated using an accelerometer. The primary endpoint of the NEXTAC-ONE study was feasibility, which was defined as the proportion of participants attending ≥4 of 6 sessions. In total, 6 pancreatic cancer patients and 24 NSCLC patients were enrolled. The median age was 75 (range, 70–84) years. In total, 29 patients participated in more than 4 of the 6 sessions (96.7, 95% confidence interval; 83.3–99.4%) and did not experience serious adverse events related to these interventions. This phase I study met the primary endpoint, and we showed a high attendance rate and satisfactory safety profile for the NEXTAC program, with high compliance rates with regard to consuming the supplements, completing the diaries, and wearing the pedometers/accelerometers. Additionally, the results suggested that the NEXTAC interventions might induce behavioral changes, with consequent improvement in the patients’ QOL [17].

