## Methods

### Study design and participants

The NEXTAC-TWO study is a multicenter, randomized phase II study with 130 participants allocated 1:1 to an intervention group or a control group. One hundred thirty patients will be recruited from 15 Japanese institutions according to the inclusion criteria and exclusion criteria listed in Table 1. Participating institutions include public hospitals, university hospitals, and cancer centers in Japan. The list of study institutions is available in Additional file 2. Recruitment began in August 2017 and is expected to be completed in July 2020.

**Table 1 Tab1:** Inclusion and exclusion criteria

Inclusion Criteria	
1) Diagnosis of advanced non-small cell lung cancer or inoperable pancreatic cancer	
2) Scheduled for systemic cancer therapy (i.e. chemotherapy, and/or targeted therapy and/or immunotherapy)	
i. In pancreatic cancer patients, planned systemic chemotherapy only allows of the combination of gemcitabine with nanoparticle paclitaxel.	
3) Eastern Cooperative Oncology Group (ECOG) performance status 0 to 2	
4) Age ≥ 70 years	
5) Body weight of 6 month ago can be confirmed	
6) An expected survival of ≥3 months as judged by investigators	
7) Written informed consent	
8) Adequate organ function	
i. Hemoglobin ≥8.0 g/dl	
ii. Total bilirubin ≤2.0 mg/dl	
iii. Aspartate aminotransferase ≤150 IU/L	
iv. Alanine aminotransferase ≤150 IU/L	
v. Serum creatinine ≤2.0 mg/dl	
vi. Arterial oxygen saturation (SpO_2_) ≥ 90% or partial pressure of oxygen in arterial blood (PaO_2_) ≥ 60 Torr in room air	
vii. Resting heart rate < 120 beat per minute	
Exclusion criteria	
1) Patients received prior chemotherapy except adjuvant chemotherapy	
2) Active malignancy requiring cancer treatment including chemotherapy, radiotherapy and surgery within 3 months	
3) Patients who need nursing care at following situation (based on Katz Index)	
i. Bathing	
ii. Dressing	
iii. Transferring	
iv. Feeding	
4) Symptomatic brain metastasis or leptomeningeal carcinoma	
5) Bone metastasis with high risk of fracture	
6) Patients who are difficult to evaluate or intervene with cardiovascular disease, bone and joint disease, neuromuscular disease etc.	
7) Patients who are difficult to participant due to psychiatric disorder	
8) Patients who are difficult to oral intake	

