### Statistical considerations

We set the recruitment period to 3 years, starting in August 2017. All participants who pass the screening are randomly assigned to the intervention group or the control group at a ratio of 1:1 in every stratified group, and they are followed for 2 years after randomization. The levels of stratification factors are as follows: (1) NSCLC or pancreatic cancer, (2) PS = 0/1 or PS = 2, and (3) cytotoxic chemotherapy or not.

With 64 patients per group, the trial achieves 80% power to detect an improvement in median disability-free survival from 8 months in the control group to 12 months in the intervention group using a two-sided log-rank test with a significance level of 0.20. Because we observed only a few dropouts from the NEXTAC program in the phase I study, we estimated the needed sample size with a small number of additional patients included. In total, 130 patients will eventually be included in the study. The disability-free survival and overall survival are estimated using the Kaplan-Meier method. To compare categorical variables, chi-square or Fisher’s exact tests are used. Continuous measures are compared using the Wilcoxon rank-sum test. For the primary endpoint analyses, *p*-values < 0.05 are considered significant.

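### Read literally, 2-year follow-up gives about 104–106 events against about 110 needed, and the 2-patient loss allowance rests on 8-week programme attendance; a common cut-off would restore the margin

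*Protocol article*

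**What the plan says.** All of the sizing is in Statistical considerations. It states "With 64 patients per group, the trial achieves 80% power". The target effect is an "improvement in median disability-free survival from 8 months in the control group to 12 months in the intervention group". The test behind this figure is described as "using a two-sided log-rank test with a significance level of 0.20". Recruitment lasts 3 years and allocation is 1:1. On follow-up it says of the participants that "they are followed for 2 years after randomization". On loss it gives this reason: "Because we observed only a few dropouts from the NEXTAC program in the phase I study, we estimated the needed sample size". The few patients added take 128 to 130. The section gives neither a required number of events nor a loss rate.

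The phase I result behind the allowance is in the section on the NEXTAC-ONE study. That was a single-arm study of an 8-week programme, and its result was "29 patients participated in more than 4 of the 6 sessions (96.7, 95% confidence interval; 83.3–99.4" percent).

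Two other places bear on when follow-up ends. Study design and participants defines the study period as lasting from enrollment to disability or death, with no 2-year limit. It also says "Recruitment began in August 2017 and is expected to be completed in July 2020". Time points of assessments and interventions sets modified Katz assessments every 8 ± 4 weeks after T4, with no end date.

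**The concern.** Log-rank power depends on the number of events, and two features of the text leave it little margin. First, if follow-up stops for each patient at 24 months, the expected events fall slightly short of what 80% power requires, even with no loss.

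Second, the only cover for loss is two patients, and its basis is the wrong quantity. Attendance at sessions of a programme over 8 weeks does not measure whether disability and death can be ascertained over 2 years. It also says nothing about the control group, which has no programme to attend. In elderly patients with advanced lung or pancreatic cancer, some loss to disability assessment should be planned for.

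With 3 years of accrual, the last patient's 2-year date falls about 60 months after the start. A 24-month stop for early entrants would discard events that occur before the final analysis can be run anyway. The risk is modest: a neutral result judged against a power a few points higher than the design provides, when the missing events could be had at little cost.

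**Working it through.** **Inputs.** From Statistical considerations: medians 8 and 12 months, two-sided alpha 0.20, power 80%, 64 per group (128) rising to 130, 36 months of accrual, 24 months of follow-up. Assumptions: exponential survival, so HR = 8/12 = 0.667 and |ln HR| = 0.4055; uniform accrual; exponential loss at the rates shown.

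**Events needed.** Schoenfeld: 4 × (1.2816 + 0.8416)² / 0.4055² = 109.7, about 110. Freedman gives 113.

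**Events under a literal 24-month stop.** Event probability is 1 − 2^(−24/8) = 0.875 for control and 1 − 2^(−24/12) = 0.75 for intervention.
- 64 per group: 64 × (0.875 + 0.75) = 104.0
- 65 per group: 65 × 1.625 = 105.6

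**Power**, Φ(√D/2 × 0.4055 − 1.2816):
- D = 104.0: Φ(0.786) = 78.4%
- D = 105.6: Φ(0.802) = 78.9%

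Log-rank simulation (20,000 runs) gives 78.6% and 79.1%; Freedman gives 77.6% and 78.1%. The stated 80% is thus reproduced to within 1–2 points by Schoenfeld and by simulation. About 135 patients would be needed to expect 110 events under this stop.

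**Common cut-off, 2 years after the last randomization** (each patient followed 24–60 months). With monthly hazard λ = ln 2/median, event probability is 1 − (e^(−24λ) − e^(−60λ))/(36λ).
- Control: 1 − (0.125 − 0.0055)/3.119 = 0.962
- Intervention: 1 − (0.25 − 0.03125)/2.079 = 0.895
- 65 per group: 65 × (0.9617 + 0.8948) = 120.7 events, power 82.8%

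**Adding loss**, N = 130. With monthly loss hazard η = −ln(1 − annual loss)/12, event probability by time T is λ/(λ+η) × (1 − e^(−(λ+η)T)), with T = 24 or averaged over 24–60.

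| Assumed loss | 24-month stop: events, power | Common cut-off: events, power |
|---|---|---|
| None | 105.6, 78.9% | 120.7, 82.8% |
| 5% per year | 101.8, 77.8% | 115.0, 81.4% |
| 10% per year | 98.0, 76.6% | 109.4, 79.9% |

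**The allowance.** 2/128 = 1.6%. In phase I, 1 of 30 (3.3%) missed the attendance criterion within 8 weeks.

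**If the effect ended at month 24.** Simulating the common cut-off without loss, with equal hazards in both arms after month 24, gives about 75–76%. The lower figure applies if both arms then run at the control hazard, the higher if both run at the intervention hazard.

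**At the other significance level.** Replacing 1.2816 by 1.960 gives 54–55% for 104–106 events and Φ(2.227 − 1.960) = 61% for 120.7 events.

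**The case against.** The strongest reply is that the stated 80% is not wrong. Without loss the gap is 1.1–1.6 points, about the spread between standard formulas. That stands: a reader might infer an arithmetic error in the sample size, and the figures do not support one.

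A reader might also take the 24-month stop as settled. It is not. The study period in Study design and participants runs to disability or death, and the Katz schedule has no end date. If 2 years is the minimum after the last entry, events exceed 110 and power without loss is 82–83%. This also stands, and it is why the passages need reconciling.

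The tempting stronger claim is that power is near 74%. That figure comes from carrying 1 in 30 per 8 weeks forward for 24 months (90.7 events, 74.2%). It implies about 36% cumulative loss and treats missed sessions as loss to endpoint follow-up, which is the very equation criticised here. The documents do not support it, and it can serve only as an extreme scenario. Scaling the sample up by 3.3% fails for the same reason.

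Finally, equal fixed follow-up is a legitimate choice, and the benefit of longer follow-up depends on an effect that outlasts a 12-week programme. That is a real cost of the remedy. An article may also leave an event target and a loss rate to the full protocol, so their absence is not the point. The point is that the reason the article does give for its allowance does not support it.

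**Conclusion.** The concern holds in a limited form. Under a literal 24-month stop, about 104–106 events are expected against about 110. Power at two-sided 0.20 is 78–79% without loss and about 77–78% with an assumed 5–10% per year. The two extra patients provide no cover for loss, because 8-week attendance in a treated arm does not measure 2-year loss to disability-free-survival follow-up in either arm. The end of follow-up is stated in two ways that must be reconciled.

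The shortfall is therefore 1–3 points; it is a thin margin rather than a failed design. It rests on exponential survival, proportional hazards, uniform accrual and loss rates that are assumptions. All these powers hold only at two-sided 0.20. The same section calls p < 0.05 significant for the primary endpoint, and at that level 104–106 events give about 55%. That conflict is larger than this one and must be settled first.

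**What to change.** 1. Settle which significance level governs the primary analysis before restating any power.
2. Replace the 2-year sentence with wording such as: all participants are followed for disability and death until 2 years after the last participant is randomized, and the primary analysis uses all follow-up to that common cut-off. Bring the study-period definition into line.
3. State the required number of events (about 110 at two-sided 0.20). Base the loss allowance on an assumed annual loss for disability-free survival, with the power that follows: about 83% without loss, 81% at 5% per year and 80% at 10% per year.
4. If the 24-month stop is kept, say so in both places and restate power as about 77–79%, depending on loss.

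**Cost.** No extra patients and no later final analysis. Routine Katz contacts continue past 24 months for those still event-free, about 24 of 130 (130 − 105.6). The gain assumes that the hazard ratio persists after month 24. If the effect vanished then, power would fall to about 75–76%, below the 78.9% of the 24-month stop, so the choice should be made and justified before any data by arm are seen.

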#### Time points of assessments and interventions

Exercise and nutritional assessment data are collected at four time points during the study period; baseline assessments are performed during the study entry until the administration of the first systemic therapeutic measure (T1 point). Systematic therapy includes cytotoxic chemotherapy, immunotherapy using an immune checkpoint inhibitor or targeted therapy using a tyrosine kinase inhibitor. These factors include stratification factors (cytotoxic chemotherapy or immunotherapy/targeted therapy). Subsequent assessment points occur at 4 ± 2 (T2 point), 8 ± 2 (T3 point) and 12 ± 2 (T4 point) weeks after randomization. After the T4 point, follow-up assessments including the determination of the modified Katz index score are performed at 8 ± 4-week intervals. In the control group, exercise and nutritional assessments are performed at the T1 and T4 assessment points. In this group, interventions are not performed at any assessment point. In the intervention group, exercise and nutritional interventions are performed at the T1-T4 points.

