## Discussion

The NEXTAC-TWO study is a multicenter, randomized phase II study evaluating the efficacy of nutritional and exercise interventions in patients with chemo-naïve advanced NSCLC or pancreatic cancer. After the baseline assessment, the participants are randomized to either the intervention group, which receives the multimodal intervention (NEXTAC program), or to the control group, which receives standard care alone.

The primary endpoint of this study is disability-free survival. We originally defined this endpoint to detect the effectiveness of the multimodal intervention with regard to enabling the patient to maintain their activity level during cancer therapy. A similar endpoint was used as the primary endpoint in a large phase III trial that investigated the efficacy of aspirin in the elderly population [25]. It is important not only to prolong survival but also to maintain elderly patients’ ability to perform daily life activities during cancer treatment. The evidence validating the use of these types of endpoints is insufficient. We will perform this trial and try to suggest a new endpoint for future supportive care trials for cancer patients. Furthermore, this trial also plans to evaluate improvements in nutritional status, physical condition, QOL, ADL, survival and safety as secondary endpoints.

Recently, anti-cachectic agents have been developed. Anamorelin, a novel ghrelin-receptor agonist, resulted in increased LBM in the ROMANA1/RONAMA2 trial [26]. However, this agent did not result a significant benefit with regard to the handgrip strength test. Those results were reproduced in the Japanese phase II trial [27]. These results suggest that additional interventions involving anti-cachectic agents will improve motor function and maintain ADL in cachexic patients. The combination of these emerging anti-cachectic agents and nonpharmacological interventions will be the next step to improve the ADL and QOL of cachexic patients. Our NEXTAC program is a promising candidate to use in combination with anti-cachectic agents.

To the best of our knowledge, this is the first randomized trial to evaluate the efficacy and safety of a multimodal intervention for elderly cancer patients involving interprofessional collaboration.

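### Continuous secondary endpoints measured at T1 and T4 in both arms are tested with no baseline covariate, which loses precision, and the article does not settle whether T1 precedes randomisation

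*Protocol article*

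**What the plan says.** Under Statistical considerations, the only method given for continuous outcomes is: "Continuous measures are compared using the Wilcoxon rank-sum test". The article names no covariate and does not say whether the T4 value or the change from T1 is compared.

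The baseline data are collected. Table 2 and the sections on time points, physical assessment and nutritional assessment schedule hand-grip strength, SPPB, QLQ-C30, CT muscle mass, MNA, food intake and body weight at T1 and T4 in both arms. Two secondary endpoints in Table 3 differ:

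- **Cumulative hospital days** have no T1 value.
- **Physical activity** is shown in Table 2 for controls at T1 but not at T4, whereas the section on time points says that controls have exercise assessments at both.

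On the timing of T1, the Discussion says: "After the baseline assessment, the participants are randomized". The section on time points says: "baseline assessments are performed during the study entry until the administration of the first systemic therapeutic measure (T1 point"). Study design and participants has patients enrolled and randomised together once they pass accelerometer screening, and Table 1 allows 14 days from enrolment to first-line therapy. According to Table 2 and the section on exercise interventions, the intervention also starts at T1.

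**The concern.** When an outcome is measured before and after treatment, the baseline value usually explains much of the variation in the later value. A two-sample rank test on T4 values does not use it, and a test on changes uses it with a fixed weight that is generally not the best one. In a trial of 130 patients the loss can matter for the secondary endpoints that would guide a later trial.

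The timing of T1 bears on the same analysis. Patients cannot be masked to counselling and exercise. If grip strength, SPPB, diet recall or QLQ-C30 is recorded at T1 after the patient knows the allocation, or after the first coaching, the value may already reflect the arm. It is then unsafe as a covariate and equally unsafe as the base for a change score. A comparison of T4 values alone is not affected.

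**Working it through.** **1. The plan's own figure.** The only stated power concerns the primary endpoint: 80% with 64 per arm, for medians of 8 (control) and 12 months (intervention), "using a two-sided log-rank test with a significance level of 0.20".

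- Hazard ratio, if exponential: 8/12 = 0.667.
- Events needed (Schoenfeld): 4 × (1.2816 + 0.8416)² / (ln 0.667)² = 110. Freedman's formula gives 113.
- Fixed 24 months per patient: event probabilities 0.875 and 0.75, mean 0.8125. This gives 128 × 0.8125 = 104 events and 78.4% power (Schoenfeld).
- 36 months' accrual plus 24 months' further follow-up: 118.8 events and 82.3% power.

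The stated 80% is thus reproduced to within about two points. It says nothing about the continuous endpoints, for which the article gives no SD, correlation or power.

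**2. Variance ratios.** Let r be the T1–T4 correlation, with equal variance σ² at both times and n patients per arm. The variance of the estimated difference between arms is:

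- T4 values: 2σ²/n
- changes: 2σ² × 2(1 − r)/n
- ANCOVA: 2σ²(1 − r²)/n

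The ratio of ANCOVA to T4 values is therefore 1 − r². The ratio of ANCOVA to changes is (1 − r²)/(2 − 2r) = (1 + r)/2. The documents give no r, so the values below are assumptions.

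| r | ANCOVA / T4 values | ANCOVA / changes |
|---|---|---|
| 0.4 | 0.84 | 0.70 |
| 0.5 | 0.75 | 0.75 |
| 0.7 | 0.51 | 0.85 |

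The inverse of a ratio gives the equivalent in patients. At r = 0.5, 1/0.75 = 1.33, or 33% more, against either comparison. At r = 0.7 it is 1/0.51 = 1.96 against T4 values, but only 1/0.85 = 1.18 against changes.

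**3. Power with the Wilcoxon test itself.** The ratios above are for mean differences, so the tests were also simulated: normal outcomes, an assumed effect of 0.4 SD, two-sided 0.05, 4,000 runs per row.

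| n per arm | r | Wilcoxon, T4 | Wilcoxon, change | ANCOVA |
|---|---|---|---|---|
| 64 | 0.3 | 59% | 45% | 64% |
| 64 | 0.5 | 60% | 60% | 74% |
| 64 | 0.7 | 60% | 80% | 87% |
| 45 | 0.5 | 45% | 45% | 59% |

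With no effect (64 per arm, r = 0.7) the rejection rates were 4.7%, 4.7% and 4.5%, so all three tests keep their level.

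The 45 per arm is an assumption. For orientation, 12 weeks is 84/30.44 = 2.76 months. Under the design medians, 64 × 2^(−2.76/8) ≈ 50 control and 64 × 2^(−2.76/12) ≈ 55 intervention patients would be alive and free of disability at T4, before other losses.

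**4. Order of events at T1.** The Discussion has assessment, then randomisation. The Methods have screening, then enrolment with randomisation, and a T1 window from study entry to first therapy. The text counts T2 to T4 from randomisation and the Table 2 footnote counts them from enrolment, which suggests that the two coincide. If study entry means enrolment, T1 follows allocation by up to 14 days. If it means consent, T1 may precede allocation. The article does not define the term.

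**The case against.** The strongest reply is that this is one sentence in a condensed article, and that covariates, effect estimates and confidence intervals commonly belong in an analysis plan that is not shown. This stands for estimates and intervals, and their absence is not part of this point. It does not remove the point, because the article does name a test for these outcomes, and that test has no place for a covariate.

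A second reply is that the text may intend changes from T1, since the Abstract and Discussion speak of evaluating improvements. That is possible, and a reader who infers that baseline is ignored altogether goes beyond the text. The loss under changes is smaller at high r, but not zero.

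Third, a rank test is defensible for bounded scales such as SPPB, MNA and QLQ-C30, in secondary endpoints of a phase II trial. That is fair. A reader might infer that the planned test is biased, but under randomisation it is valid, and the simulation bears this out.

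Fourth, the timing passages can be read together: assess, randomise, intervene, all before first therapy. That sequence would satisfy both the Discussion and the T1 window. The documents therefore do not show that baselines were taken after allocation, only that the Methods permit it.

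**Conclusion.** The point holds as one of precision and clarity in secondary endpoints. It covers the seven measures taken at T1 and T4 in both arms. It does not cover every continuous endpoint: hospital days have no baseline, and physical activity cannot be placed until the control-arm T4 measurement is settled.

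For assumed r of 0.4 to 0.7, adjustment lowers the variance to 0.84–0.51 of that for T4 values, or 0.70–0.85 of that for changes. These figures rest on assumed correlations, equal variances and normal theory; no loss can be read from the documents. In particular, a near doubling of the sample-size equivalent needs both r = 0.7 and a comparison of T4 values only, and the article states neither. No planned sample size changes, because none is set for these endpoints.

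The ambiguity about T1 is real. It matters for an adjusted analysis and for change scores alike.

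**What to change.** **Analysis.** For the seven measures, replace the sentence with: ANCOVA of the T4 value on arm, T1 value and the stratification factors actually used, with a rank-based ANCOVA or a proportional-odds model for skewed or ordinal scales, and the Wilcoxon test as a sensitivity analysis. First settle those factors, since the Abstract lists four, including stage, and Statistical considerations lists three, without stage. Hospital days stay unadjusted for baseline. For physical activity, reconcile Table 2 with the section on time points before choosing an analysis.

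**Timing.** Reconcile Study design and participants, Table 2 with its footnote, the section on time points and the Discussion, so that T1 outcome measures are taken before randomisation and before the first intervention session. For patients already enrolled, check the date of each T1 measure against randomisation and add a sensitivity analysis that excludes post-allocation baselines.

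**Cost.** The analysis needs no new data and only slightly more work. The timing change is not just a reordering within screening, because the T1 window can extend past enrolment and the T1 visit also delivers the intervention. Separating measurement from that session needs minor scheduling. Recruitment was ongoing when the article was written, so the change reaches only later patients.
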